## Abstract

**Background:**

Two thirds of the global mortality of stroke is borne by low and middle income countries (LMICs). Pakistan is the world’s sixth most populous country with a stroke-vulnerable population and is without a single dedicated chronic care center. In order to provide evidence for a viable solution responsive to this health care gap, and leveraging the existing >70 % mobile phone density, we thought it rational to test the effectiveness of a mobile phone-based video intervention of short 5-minute movies to educate and support stroke survivors and their primary caregivers.

**Methods:**

Movies4Stroke will be a randomized control, outcome assessor blinded, parallel group, single center superiority trial. Participants with an acute stroke, medically stable, with mild to moderate disability and having a stable primary caregiver will be included. After obtaining informed consent the stroke survivor-caregiver dyad will be randomized. Intervention participants will have the movie program software installed in their phone, desktop, or Android device which will allow them to receive, view and repeat 5-minute videos on stroke-related topics at admission, discharge and first and third months after enrollment. The control arm will receive standard of care at an internationally accredited center with defined protocols. The primary outcome measure is medication adherence as ascertained by a locally validated Morisky Medication Adherence Scale and control of major risk factors such as blood pressure, blood sugar and blood cholesterol at 12 months post discharge. Secondary outcome measures are post-stroke complications and mortality, caregiver knowledge and change in functional outcomes after acute stroke at 1, 3, 6, 9 and 12 months. Movies4Stroke is designed to enroll 300 participant dyads after inflating 10 % to incorporate attrition and non-compliance and has been powered at 95 % to detect a 15 % difference between intervention and usual care arm. Analysis will be done by the intention-to-treat principle.

**Discussion:**

Movies4Stroke is a randomized trial testing an application aimed at supporting caregivers and stroke survivors in a LMIC with no rehabilitation or chronic support systems.

**Trial registration:**

NCT02202330 (28 January 2015)

**Electronic supplementary material:**

The online version of this article (doi:10.1186/s13063-016-1175-x) contains supplementary material, which is available to authorized users.

## Background

The World Health Organization (WHO) defines stroke as “a focal (or at times global) neurological impairment of sudden onset, and lasting more than 24 hours (or leading to death) and of presumed vascular origin” [1]. Two thirds, i.e., 36 million of the estimated 56 million deaths worldwide are attributed to non-communicable diseases (NCD), primarily stroke. Over 80 % of strokes now occur in LMICs [2], with 15 million strokes occurring annually worldwide, leaving five million dead, and five million permanently disabled. One person suffers a stroke every 45 seconds; one person dies of a stroke every 4 minutes [3]. Globally, stroke accounts for 46.6 million disability adjusted life-years (DALYs) [4].

NCD and stroke are becoming an important issue in Pakistan as the country undergoes demographic transition [5]. Pakistan, the sixth most populous nation in the world, has a distinctively stroke-prone population. Today, about one in four adult Pakistanis has hypertension and/or diabetes, heart disease, or a stroke equivalent [6]. Yet, early detection and risk reduction would have prevented stroke in 80–90 % of victims [7]. A local study conducted on one ethnicity (Pashtoon), reported a prevalence of 4.8 %, which would translate into four million persons in a country of 180 million [6]. In another hospital-based study, 65 % of adult Pakistani stroke survivors reported at least one post-stroke complication and a 12 % mortality in the first year post discharge [8].

This high-risk population is also highly underserved. Health systems are acutely responsive and are not equipped to respond to chronic diseases. There is not a single inpatient comprehensive rehabilitation system. Since the recent democratic reforms and 18th Constitutional Amendment, an opportunity has arisen for health reform, where devolution has resulted in provincial autonomy for health [9]. Thus, evidence for a systematized, replicable, scalable and effective response to chronic disorders is much more likely to be adapted.

In 80 % of stroke victims, further events may be prevented by altering lifestyle risk factors, and increasing adherence to medications to control hypertension, diabetes and hyperlipidemia [10–12]. However, there exists an implementation gap to adopt widely recognized beneficial medicines and lifestyle changes after stroke [6].

In this study, we will assess the effect of video-based intervention on primary stroke survivors and their caregiver dyads on improving adherence to stroke preventive medications and control of three major risk factors at 6 and 12 months in a Pakistani population. Our rationale is to leverage the existing mobile phone infrastructure and use IT to deliver post-stroke education to dyads returning to the community and thereby improve post-stroke outcomes. We hypothesize that there would be a difference of at least 15 % in adherence to stroke preventive medications and control of three major risk factors at 6 and 12 months among stroke survivors who are given video-based education as compare to those who are given usual care.

### Study question

Does video-based intervention given to stroke survivors (with mild to moderate disability) and their caregivers at the time of enrollment into the study, at discharge and sustained during follow-up, improve adherence to stroke preventive medications and control of three major risk factors (diabetes, hypertension and dyslipidemia) at 6 and 12 months after first ever stroke?

### Primary objective

To determine the effect of video-based education intervention provided to patient and caregiver dyads after first ever stroke on:Proportion of participants adhering to medications prescribed (definition of adherence is the use of prescribed medications on at least 5 days a week and measured by the Morisky Medication Adherence Scale)Proportion of participants achieving control of blood pressure (control is defined as BP <125/85), blood sugar (glycosylated hemoglobin (HbA1c) <7 %) and blood cholesterol (low-density lipoprotein cholesterol (LDL) <100 mg/dl)

### Secondary objective

To determine the effect of video-based education intervention provided to patient and caregiver dyads after first ever stroke on:Stroke-related knowledge assessment among caregivers regarding risk factors, emergency preparedness, stroke rehabilitation and medicationsReadmission to hospital with any of the stroke-related complications – urinary tract infection, pneumonia, and deep venous thrombosis, among stroke survivors admitted to the AKUH Stroke Unit, KarachiStroke-related mortality among stroke survivors with mild to moderate disability admitted to the AKUH Stroke Unit, KarachiChange in functional outcome (severity and disability after stroke) from baseline among stroke survivors admitted to the AKUH Stroke Unit, KarachiLevel of satisfaction with the intervention and acceptability of mobile health (mHealth) innovations by stroke survivor and caregiver dyads

## Methods

### Study design

This will be a randomized controlled, outcome assessor blinded, parallel group, single center superiority trial in which participants with first ever stroke (both ischemic and hemorrhagic) will be randomized within 48 hours of their stroke to either the video-based education intervention group or the control group [13]. The video-based education intervention group will have health education delivered through short videos which will be shown to the participants and their caregivers at the time of admission, before discharge, and follow-up at first and third month post discharge. The control group will have standard care including pre-discharge education and counseling according to defined protocol. All participants enrolled in this video education intervention group and control group will be followed for 12 months post discharge for assessment of end-points (Refer to Fig. 1).

**Fig. 1 Fig1:**
[figure not shown]
Study flow chart

### Study setting

The trial will be conducted in the Stroke Unit, Neurology ward at Aga Khan University Hospital (AKUH) Karachi, Pakistan. AKUH is an internationally recognized tertiary care institution certified by Joint Commission International Accreditation (JCIA) that caters to the needs of large multi-ethnic urban population of 18 million.

Due to the high variability of stroke care being delivered in different centers of Karachi and the need to evaluate a complex multimodal intervention against a uniform standard of care, we chose to limit our study to a single center. Usual care at AKUH involves a proper stroke pathway which includes a standard protocol being followed by a neuro-physician, a stroke nurse, a dietitian and a physiotherapist in accordance with institutional guidelines (please refer to Standard Care for Stroke Survivors for details).

### Population

The following criteria will be used while recruiting participants and caregivers throughout the study:

### Stroke survivor

Any adult aged 18 years of age or older, having experienced first ever stroke (ischemic or hemorrhagic) within the past 6 weeks, with mild to moderate disability. Stroke is clinically stable and the stroke survivor is returning to the community for chronic care.

### Caregiver

An adult aged 18 years of age or older who is present 24 hours a day with the stroke survivor and provides the overall day-to-day care of the stroke survivor, including acute emergency care, appointments, and/or follow-up visits.

### Android mobile

Any portable telecommunication device based on the Android Operating System, in the possession of either the stroke survivor or the caregiver, which is compatible with our Movies4Stroke Application.

### Eligibility criteria

#### Inclusion criteria

Adult men and women, 18 years of age or olderResident of Karachi and planning to live in Karachi till the follow-up periodAble to understand Urdu (language of the videos)Admitted with first ever stroke (ischemic or hemorrhagic stroke)Modified Rankin score (mRS) ≤4 ( mild to moderate stroke)Have at least one vascular risk factor that requires medical interventionConsenting to participate in the study and follow-up, both stroke survivor and caregiverHave a stable surrogate caregiver at home who is responsible for appointments, follow-ups, overall care, e.g., wife, daughters, daughter- in- law, husbandStroke is medically stable and participant is likely to return to the community after the in- hospital stay (thus, actively treated strokes, e.g., decompressive surgeries, carotid endarterectomy (CEA), in-hospital sepsis, ventilator complications) that essentially preclude return to the community settings will not be offered this chronic care support study

### Exclusion criteria

Serious aphasia, visual hemi-neglect, short-term memory loss in the stroke survivor precluding understanding, visualization or retention of the video material (will be measured through the NIH Stroke Scale performed by trained physicians; those having a score of greater than 4 due to aphasia alone will be excluded)Serious aphasia, visual hemi-neglect, short-term memory loss, dementia in the caregiver precluding understanding, visualization or retention of the video material (will be measured through the NIH Stroke Scale performed by trained physicians; those having a score of greater than 4 due to aphasia alone will be excluded, dementia status will be assessed by the Mini-Mental State Examination)Iatrogenic stroke, i.e., stroke due to non-atherosclerotic vascular disease and rare causes, e.g., carotid dissections, gunshot wounds to the neck, post coronary artery bypass grafting (CABG)Stroke survivor/Caregiver dyad continue post-stroke care in a nursing assisted, professional or hospital setting and do not return to the community after dischargeSerious concurrent medical illnesses, like cancer, renal failure, acute liver disease in past 6 months (that precludes the use of statins), chronic liver disease that excludes the use of stroke preventive medications, or require non-standardized therapyUse of any off-label, non-guideline medications which, due to stroke survivors’ unique co-morbidities, interfere with medication compliance to antihypertensives, statins, antiplatelet agents and diabetes control

### Identification and enrollment of the study participants

Data collectors will screen the participants coming to AKUH Stroke Unit, Neurology ward, Karachi. Data collectors will fill out the eligibility form and, if the participants are found eligible for the study, they will be officially invited to participate in the trial. Informed consent will be obtained from those participants who voluntarily wish to be in our study. The study participants and their caregivers will be thoroughly counseled about the nature of the study and required follow-up. It will also be explained to study participants that the selection in the study group is random. Stroke survivors will then undergo a detailed interview regarding the socio-demographic, clinical and functional assessment at baseline. Then, the participants will undergo randomization to either the intervention group or standard care group. After allocation assignment, the research supervisor will thoroughly explain the details of the software program and its installation and then proceed with the delivery of the first set of 5- minute videos. Any questions pertaining to the use and the comprehension of the videos and software will be answered. Videos will be shown at the time of enrollment into the study, at discharge from the hospital, and follow-up at first and third months post discharge and a memory card containing the Stroke4Movie Application will be installed and programmed to deliver scheduled videos on the participant’s Android phone. In case of the participant being allocated to the usual care group they will be informed about the details regarding discharge and the follow-up appointments at the clinic (Refer to Fig. 2) (see Additional files 1, 2 and 3).

**Fig. 2 Fig2:**
[figure not shown]
Template for screenshot of short messaging service (SMS)

### Sampling technique

A purposive sampling technique would be applied to select adult stroke survivors coming to the Stroke Unit, Neurology ward, AKUH, Karachi after the assessment of the eligibility criteria and informed consent. The purposive sampling technique is defined as the sample based on researchers’ established criteria for eligibility. Access to daily admission lists of stroke patients to all areas of the hospital will serve as the reference sampling frame for this exercise.

### Randomization process

A computer-generated random number list will be used to randomize subjects to the control arm or the intervention arm. The randomization center will be at a secure computer in the Clinical Trials Unit (CTU) and the random number will be generated by the staff of the CTU who are not involved in recruitment and/or outcome ascertainment.

### Allocation concealment

Randomization sequence will not in any way be predictable as it will be centralized. No-one from the research team will have access to the randomization sequence, block size, randomization envelopes or code. Envelopes will be sealed, opaque and it will be impossible to view the code even if it is held against bright sunlight.

### Sample size calculation

The study is designed to enroll 300 participant dyads (150 participants and 150 caregivers in each group – intervention versus standard care) after inflating 10 % to incorporate attrition and non-compliance. The sample size was calculated keeping in mind the two primary end-points of medication adherence and risk factor control; the primary end-point that gave the highest sample size was kept as the final sample size. This number of participants would provide the study with the ability to detect a 15 % difference among groups with a power of at least 95 %. The proportion of participants achieving control of three modifiable risk factors (blood pressure, blood cholesterol and blood sugar) was assumed to be 0.50 in the treatment group and 0.350 in the control group. The test statistics used was a two-sided *Z* test. The sample size was calculated using NCSS PASS (version 2008).

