### Statistical analysis plan

Analysis will be performed on the basis of initial treatment allocation; that is the intention-to- treat (ITT) principle.

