While there is a relative lag in development of such centers, we plan to test and leverage our existing mobile infrastructure as a means of providing continuous care. Based on the current statistics by the Pakistan Telecommunication Authority, mobile phone users in Pakistan were recorded to number greater than 137 million and total cellular density had reached 77 % by 2014 [35]. In addition, mobile brands have introduced cheap Android Smart phones that are rapidly becoming mainstream and are expected to take over the larger market share, with the cheapest Smart phone starting from around US$6 [25]. Thus, we developed this interactive Android application.

mHealth applications have tremendous potential for chronic disease support. However, these software applications have not been tested in rigorous trial designs with clinically meaningful outcomes [36–38, 39].

The strength of this study is the use of a rigorous randomized controlled trial (RCT) design, measurement of intervention usage and fidelity, intervention delivery that is present both within the hospital and at follow-up, evaluation of clinically important outcomes and ITT analysis [40].

The limitations include the following: selection bias: this is a single center study chosen because of the fact that this site provides a standard of care that is algorithmic and replicable; thus, any results may be attributed to the intervention. In this study we may report its efficacy, but the performance in different sites may vary; contamination bias: in an educational intervention, care will have to be taken to avoid contamination of the non-intervention arm with the intervention. To ensure this, videos will be shown in a separate room, and not at the bedside. Given the fact that families do share information, contamination is possible; however, most stroke participants are on different schedules for visits, rehabilitation times, etc. and so we expect less contamination than in areas where a lot of time is spent together by families; attrition bias: many participants may drop out due to the longitudinal nature of the study. To counteract this, trained health care providers will try to follow the subjects closely through regular phone calls and build good rapport with them. A Stroke Helpline number will also be provided.

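### The 95 % power claimed for 150 per arm is about 75 % before any loss, and a 10 % allowance below the protocol's own 12 % mortality figure makes the shortfall slightly worse

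*Protocol article*

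**What the plan says.** All design inputs stand in the protocol article under Sample size calculation. The enrolled number is 300 dyads, described as "150 participants and 150 caregivers in each group", reached "after inflating 10 % to incorporate attrition and non-compliance". The section claims the "ability to detect a 15 % difference among groups with a power of at least 95" %. The proportion with risk-factor control "was assumed to be 0.50 in the treatment group and 0.350 in the control group". On the test it says: "The test statistics used was a two-sided *Z* test". No alpha is given there. The abstract repeats the 95 % and the 15 % difference.

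Three other places bear on the allowance:

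- The Background cites a hospital-based study of adult Pakistani stroke survivors with "a 12 % mortality in the first year post discharge". The trial also follows participants for 12 months after discharge.
- The Discussion, under attrition bias, concedes that "many participants may drop out due to the longitudinal nature of the study" and gives no figure.
- Outcome assessment removes from the final analysis any participant whose assessor was unblinded, again without a figure.

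On the analysis set, the Statistical analysis plan section says: "Analysis will be performed on the basis of initial treatment allocation".

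**The concern.** Two things do not fit. First, a two-sided test of 0.50 against 0.35 with 150 per arm looks far too small for 95 % power. Second, a single 10 % has to absorb death, drop-out and non-compliance, while the only loss figure in the document is 12 % for death alone over the same 12 months. Nothing is left for the drop-out that the Discussion expects or for the removals after assessor unblinding.

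There is also a problem of kind. Under intention to treat, a non-complier is not lost. That person stays in the analysis and shrinks the observed difference. The required number grows roughly with the inverse square of the effect, so adding the same percentage to N does not repair the dilution.

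The interpretation of the result is at stake. A null finding from a trial described as having 95 % power reads as good evidence against a 15-point effect. From a trial with about 70 % power it does not.

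**Working it through.** **Inputs.** p1 = 0.50, p2 = 0.35, 1:1 allocation, 150 per arm and a two-sided Z test (Sample size calculation); 12 % mortality (Background). Alpha = 0.05 two-sided is an assumption. In the document 0.05 appears only as the significance level for the multivariable model.

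**Formula (pooled Z test, n per arm).**

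Power = Φ{ [ |p1 − p2|·√n − z(0.975)·√(2·p̄·(1 − p̄)) ] / √(p1(1 − p1) + p2(1 − p2)) }

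- p̄ = (0.50 + 0.35)/2 = 0.425, so √(2 × 0.425 × 0.575) = √0.48875 = 0.6991
- √(0.25 + 0.2275) = √0.4775 = 0.6910
- z(0.975) × 0.6991 = 1.960 × 0.6991 = 1.370

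**Step 1: the protocol's own claim.** With n = 150 and no loss, 0.15 × √150 = 1.837, and (1.837 − 1.370)/0.6910 = 0.676. Power = 75.0 % (75.8 % with unpooled variance). The stated 95 % does not reproduce. Other readings of the test:

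| Reading | Power |
|---|---|
| 150 per arm, one-sided 0.05 or two-sided 0.10 | 84.0 % |
| 150 per arm, one-sided 0.10 | 91.3 % |
| 300 per arm, two-sided 0.05, no loss | 96.2 % |
| 270 per arm (300 less 10 %), two-sided 0.05 | 94.3 % |

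No alpha tried brings 150 per arm to 95 %. Only taking 300 as the number per arm comes near, and the text says 150 per group.

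**Step 2: number needed for 95 %.** n = [(1.370 + 1.645 × 0.6910)/0.15]² = (2.507/0.15)² ≈ 279.3, so 280 evaluable per arm. Enrolment would be 280/0.90 → 312 per arm (624 in total) at 10 % loss, or 280/0.88 → 319 per arm (638) at 12 %.

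**Step 3: effect of the allowance.** The protocol states no evaluable number. Its text implies 300 × 0.90 = 270, or 300/1.1 ≈ 273.

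| Loss | Per arm | Power |
|---|---|---|
| 0 % | 150 | 75.0 % |
| 10 % (planned) | 135 | 70.5 % |
| 12 % (cited mortality alone) | 132 | 69.5 % |
| 17 % (12 % plus an assumed 5 %) | 124.5 | 67.0 % |
| 22 % (12 % plus an assumed 10 %) | 117 | 64.2 % |

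Moving from 10 % to 12 % costs 270 − 264 = 6 participants and 70.5 − 69.5 = 1.0 point of power.

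**Step 4: non-compliance as dilution (an assumption, for illustration).** If 10 % of the intervention arm gain nothing, the treated proportion is 0.35 + 0.9 × 0.15 = 0.485. At 135 per arm, 0.485 against 0.35 gives 61.5 %; at 132 per arm, 60.5 %.

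**Step 5: if deaths are kept and counted as not controlled.** At 12 % mortality in both arms the proportions are 0.88 × 0.50 = 0.44 and 0.88 × 0.35 = 0.308. With all 150 per arm kept, power is 65.8 %. Retaining the deaths in this way does not recover the power either.

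**The case against.** A reader might infer that the 10 % allowance is why the trial misses 95 %. The figures do not support that. The gap from 95 % to 75 % exists with no loss at all, and replacing 10 % by 12 % adds about one point. A reader might also infer that the protocol overstates its evaluable number. It states none, and the implied 270 would fall only to 264.

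Nor can the 12 % be taken as this trial's death rate. It is background from another hospital cohort whose case mix the document does not describe. The eligibility criteria require a first stroke, medical stability, a caregiver at home and likely return to the community. They exclude serious concurrent illness. Lower mortality is plausible, so the document does not show that the 10 % must fail. On the other side, the trial admits both stroke types and mRS up to 4, and offers no lower figure.

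Drop-out is also mitigated. The protocol plans phone calls, a helpline, SMS reminders, arranged transport and a ±14-day window. Supervised viewing of each video limits complete non-receipt of the intervention. Adherence, the other primary end-point, is a questionnaire measure and needs no laboratory values. HbA1c is taken only in diabetics, and the study question also names 6 months, when fewer deaths would have occurred. The 5 to 10 % extra loss and the 10 % non-compliance used in the working are illustrations and not figures from the protocol.

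These objections limit what can be said about the allowance. They do not touch the main discrepancy, which needs no loss assumption. The adherence end-point does not rescue the claim either: the section says that the end-point needing the larger number fixed the sample size, so 300 should at least suffice for risk-factor control.

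**Conclusion.** The claim of at least 95 % power is wrong on the protocol's own inputs. At two-sided alpha 0.05 the design gives about 75 % with no loss and about 70 % with 10 to 12 % loss, a shortfall of 20 to 25 points. This rests on the assumed alpha and on taking 150 per arm as written. The size of the gap changes with alpha, but none of the levels tried (0.05 and 0.10, one- and two-sided) closes it.

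The allowance is a secondary weakness, worth about one point of power on mortality alone. The only loss figure in the document exceeds an allowance meant to cover attrition and non-compliance together, and nothing is left for drop-out or unblinding removals. The 12 % should be read as a caution about the 10 % and not as a forecast. Treating non-compliance as loss is a separate error of method under intention to treat. Its cost depends on a rate that the protocol does not give.

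**What to change.** Keep N = 300 and correct the text.

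1. Under Sample size calculation and in the abstract, replace the 95 % by the power delivered for 0.50 against 0.35: about 75 % with no loss and about 70 % with 10 to 12 % loss. State the alpha used.
2. State the evaluable number: 270 at 10 % loss, 264 at 12 %.
3. Separate the components of the allowance. Treat deaths and drop-out as loss, with the cited 12 % mortality as a sensitivity value and drop-out as a stated assumption. Mention the removals after assessor unblinding.
4. Treat non-compliance as dilution of the 15-point effect. An example is 10 % with no benefit at 135 per arm, about 61 % power, labelled as an assumption.

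The cost is a rewritten paragraph and one line of the abstract, with no extra participants. The drawback is a less favourable stated power. If the sponsor wishes to keep the 95 % claim instead, about 280 evaluable per arm are needed, or 624 to 638 enrolled at 10 to 12 % loss.

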### Multivariable analysis

A variable having a *p* value of less than or equal to 0.05 will be considered to be clinically significant as well as statistically significant at the multivariable analysis level. All variables that are considered to be significant at the univariate analysis level will need to run through a stepwise model building approach (manual) to obtain a parsimonious model. Multiple linear regression (MLR) will be used to predict the final model. Adjusted beta-coefficients with their appropriate 95 % confidence interval will be reported for the final model. The final model will be assessed for interaction between biologically plausible variables as well as for confounding after checking for interaction; beta-change (15 %) will be considered significant for confounding to be reported. Assessment of multicollinearity between two independent variables will be carried out using appropriate statistical tests. A correlation coefficient of more than 0.80 will be treated as significant for multicollinearity. The model will be assessed for the presence of outliers and influential observations and robust standard errors will be reported if influential observations are found.

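### At 0.50 versus 0.35, 150 survivors per arm give about 75 % power (two-sided alpha 0.05 assumed), not the stated 95 %

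*Protocol article*

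**What the plan says.** The Sample size calculation section fixes almost everything needed to check the power for risk factor control.

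- Size: "The study is designed to enroll 300 participant dyads (150 participants and 150 caregivers in each group", a figure reached "after inflating 10 % to incorporate attrition and non-compliance".
- Power: the "ability to detect a 15 % difference among groups with a power of at least 95" per cent.
- Rates: control of the three risk factors "was assumed to be 0.50 in the treatment group and 0.350 in the control group".
- Test: "The test statistics used was a two-sided" Z test.
- Two primary endpoints were considered, and "the primary end-point that gave the highest sample size was kept as the final sample size". No rates are given for medication adherence.

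The Methods paragraph of the Abstract repeats that the trial "has been powered at 95 % to detect a 15 % difference between intervention and usual care arm".

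The sample size section does not state alpha. The nearest threshold is in Multivariable analysis, where a p "value of less than or equal to 0.05 will be considered to be clinically significant as well as statistically significant".

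**The concern.** A 15-point difference near the middle of the probability scale is expensive to detect, and 150 per arm is well short of what 95 % power normally takes there. The power, the sample size and the assumed rates cannot all be right.

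The consequence falls on how a null result is read. Someone who trusts the article would take a non-significant comparison of risk factor control as strong evidence against a 15-point benefit, believing the risk of a miss to be at most 5 %. If the true risk is five to six times that, the inference is unsafe. The Discussion makes a larger study conditional on encouraging results from this one, so a false negative could end the programme on a misjudged basis.

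**Working it through.** **Inputs.** From Sample size calculation: p1 = 0.50, p2 = 0.35, difference 0.15, two-sided Z test, n = 150 survivors per arm, 10 % allowance. Assumed: two-sided alpha 0.05 (z = 1.960), with other values tried below. The survivor is the unit, because blood pressure, HbA1c and LDL are measured on the survivor only (Outcome assessment; Primary study outcomes).

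**Formula** (pooled variance under the null, unpooled under the alternative):

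power = Φ{ [δ − z·√(2·p̄·(1−p̄)/n)] / √([p1(1−p1) + p2(1−p2)]/n) }

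Here p̄ = 0.425, so 2·p̄·(1−p̄) = 0.48875, and p1(1−p1) + p2(1−p2) = 0.25 + 0.2275 = 0.4775.

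**Attempt to reproduce the stated figure, n = 150.** The standard errors are √(0.48875/150) = 0.05708 and √(0.4775/150) = 0.05642. Then (0.15 − 1.960 × 0.05708)/0.05642 = 0.676, and Φ(0.676) = **0.750**. The stated 0.95 is not reproduced.

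**After the plan's 10 % loss, n = 150 × 0.9 = 135.** The standard errors are 0.06017 and 0.05947. Then (0.15 − 1.960 × 0.06017)/0.05947 = 0.539, and Φ(0.539) = **0.705**. Reading the inflation as 300/1.1 leaves 136 per arm and gives 0.708.

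**Sample size for 95 % power.** n = [1.960·√0.48875 + 1.645·√0.4775]² / 0.15² = (1.3702 + 1.1366)²/0.0225 = 279.3, so **280 evaluable per arm**, 560 in all. With losses this is 280/0.9 = 312 per arm (624 in all), or 280 × 1.1 = 308 per arm (616) if the 10 % is added on. The same formula gives 170 per arm for 80 % power and 227 for 90 %.

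**Does another method or alpha rescue 95 %?**

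| Variant (0.50 v 0.35) | 150 per arm | 135 per arm |
|---|---|---|
| Pooled Z, two-sided 0.05 | 75.0 % | 70.5 % |
| Unpooled Z | 75.8 % | 71.3 % |
| Arcsine | 75.1 % | 70.7 % |
| Exact power of the pooled Z test | 76.1 % | 71.1 % |
| Continuity-corrected | 71.1 % | 66.1 % |
| Pooled, two-sided 0.025 | 65.2 % | 60.0 % |
| Pooled, one-sided 0.05 (= two-sided 0.10) | 84.0 % | 80.5 % |
| Pooled, two-sided 0.20 | 91.3 % | 89.0 % |

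Solving for the alpha that gives 95 % at n = 150: z = (0.15 − 1.645 × 0.05642)/0.05708 = 1.002, a two-sided alpha of about 0.32. At 135 per arm it is about 0.39.

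**What 95 % power does buy.** Against a control rate of 0.35, the detectable difference is about 20.5 points with 150 per arm and about 21.6 points with 135. As a bracket, at 150 per arm power is 94.0 % for 20 points and 95.8 % for 21. At 135 per arm it is 93.8 % for 21 points and 95.6 % for 22.

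**A possible origin, by inference only.** With 300 independent survivors per arm the formula gives 96.2 %. Counting both dyad members (150 + 150 in each group), or entering the total as a per-arm number, would produce a figure of that kind. The text cannot settle this, and the shortfall does not depend on it.

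**The case against.** *Alpha is not given.* True, so 75 % and 71 % are conditional on an assumed 0.05; the 0.05 in Multivariable analysis concerns model terms. This qualifies the exact figures but not the conclusion, since even two-sided 0.20 leaves power at 91 %.

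*The 95 % may describe medication adherence.* Power for a 15-point difference depends on the base rate, and no adherence rates are given. With 150 per arm, a 15-point difference reaches 95 % if the lower rate is about 0.08 or below, or about 0.77 or above. So the 25 to 29 % risk of a miss is shown for risk factor control only and should not be extended to adherence. But this does not save the statement. The section says the more demanding endpoint set the size. Had that been adherence, risk factor control would have needed no more than the chosen number for the same power, whereas it needs 280 per arm.

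*The 10 % covers non-compliance as well as attrition.* Under intention to treat, non-compliers stay in and dilute the effect, so treating the whole 10 % as lost observations is an approximation. It is not a harsh one. Suppose instead that 10 % of the intervention arm respond at the control rate: the rate becomes 0.9 × 0.50 + 0.1 × 0.35 = 0.485 and the difference 0.135. At 150 per arm the standard errors are 0.05694 and 0.05641, and Φ[(0.135 − 1.960 × 0.05694)/0.05641] = Φ(0.415) = 0.66.

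*The wrong number might be the sample size or the rates rather than the power.* The article cannot show which. This stands as a reason to look at the original software run first.

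**Conclusion.** The statement of at least 95 % power is wrong on the article's own inputs. For risk factor control at 0.50 versus 0.35, power is about 75 % with 150 survivors per arm and about 71 % with 135, a shortfall of 20 and 24 percentage points. The stated power would need 280 evaluable survivors per arm, nearly twice the number planned (280/150 = 1.87).

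The exact figures rest on two-sided alpha 0.05, which is assumed, on equal arms, and on the survivor as the unit. The conclusion that 95 % is not reached holds for every formula and every conventional alpha tried. Nothing elsewhere in the article corrects the figure. It must be fixed, because it is the trial's main claim about what it can detect.

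**What to change.** Rerun the stored sample size calculation and report all its inputs, including alpha, so that the source of the error is known. Then, since the trial is under way, keep 300 dyads and correct the power statement in Sample size calculation and in the Abstract's Methods paragraph. Suggested content:

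- With 150 stroke survivors per arm and two-sided alpha 0.05, power to detect 0.50 versus 0.35 in risk factor control is about 75 %, and about 71 % with the 135 per arm expected after 10 % loss.
- Power of 95 % applies only to a difference of about 21 points from a control rate of 0.35.
- The survivor is the unit of analysis for this endpoint; caregivers do not add to n.

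The cost is a few sentences and a less favourable stated power, with no extra patients. If the team wants to keep the 95 % target at these rates, the alternative is 280 evaluable survivors per arm, about 616 to 624 dyads in all once the 10 % allowance is added, roughly double the planned enrolment. If the rerun shows that the rates were mis-transcribed, the rates should be corrected instead and the power recomputed from them.
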